### Assignment of Interventions

#### Sequence Generation

At recruitment, 60% of participants will be randomized to the MRT. The remaining participants will be randomly allocated 50:50 to receive no notifications or to receive standard notifications daily at 11 am.

Among the participants randomized to the MRT, at 8 pm each participant will be randomized daily to receive one of three options: no notification, the standard notification wording, or a message randomly selected from the new message bank. The randomization probabilities for these three options will be 40%, 30%, and 30%, respectively.

The randomization probabilities are fixed across all individuals and do not depend on individuals’ time-varying treatment, outcomes, or covariates.

#### Allocation Concealment Mechanism

Users will be aware of whether or not they have received a push notification each day. They will be informed in the consent procedures that they are part of a research study testing how different versions of the app affect use. However, they will not receive explicit information that we are interested in the effect of the notification, about which arm of the study they have been allocated to, the full design of the study, or the planned schedule of their notifications. The standard request for users to enable notifications at the end of the onboarding process was disabled for this trial.  Users were still able to turn off the notifications through their phone settings.

#### Implementation

Simple randomization was used, with no stratification or blocking. The code to generate the randomization sequencing was developed and coded into the app by an external app developer. Members of the trial team verified the randomization process.

### Data Collection, Management, and Analysis

Descriptions of the trial participants, in terms of their available baseline data, will be reported for all MRT participants and participants in the two additional arms.

#### Primary Analysis (MRT)

Our primary analysis will estimate the marginal effect of the notifications on the binary, time-varying outcome of whether or not a user opens the app between 8 pm and 9 pm. The marginal effect is averaged over all days and all participants in the MRT arm.

The effect of notifications, quantified as a relative risk, with a 95% confidence interval, will be assessed using the estimator for marginal excursion effect for MRTs with binary outcomes [45]. The excursion effect is a causal effect concerning what would happen if an individual followed the notification scheduled used in the MRT up to day *t–*1 and then deviated from the schedule to receive a notification at day t, versus deviated from the schedule to receive no notification at day *t*. The notification schedule used in the MRT is the delivery of push notifications with 40%, 30%, 30% probability every evening at 8 pm (see the last paragraph of the subsection Trial Design). The marginal excursion effect we consider in the primary analysis will marginalize (ie, average) overall days and all individuals. Because the near-term outcome is binary, we will estimate the marginal excursion effect on the log relative risk scale.

For this analysis, both types of notification—the standard wording and the messages drawn from the new bank of messages—will be pooled; the comparison will be between any notification versus no notification. *P* values less than .05 will be considered statistically significant. Models used in the primary and secondary analyses for the MRT arm will adjust for age, gender, employment type, baseline AUDIT score, the number of days since download, if the user opened the app before 8 pm, and if the user opened the app the day before.

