#### Secondary Objectives

The secondary objectives are as follows:

Compare the marginal effect of the new bank of 30 messages to the standard wording of “Please complete your mood and drinking diary” on near-term engagement, defined as the use of the app in the hour following the notification decision point (8 pm to 9 pm).Explore whether the effect of a notification (pooling both types of messages) on near-term engagement decreases over time.Estimate the lagged effect of prior notifications on near-term engagement.Understand how the notification effect is moderated by time-varying covariates (use before 8 pm, use on the previous day, weekend/weekday effect).Investigate if the effect of the notifications depends on baseline characteristics (gender, age, employment type, AUDIT score).Examine overall engagement during the 30 days following download in users receiving no notifications, those who receive the standard notification daily at 11 am, and those who receive a mix of notifications at 8 pm.

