### Outcomes

#### Primary Outcome (MRT)

The primary outcome measure in the MRT is a time-varying, binary proximal (ie, near-term) measure of engagement (use of the app). Specifically, the primary outcome for the MRT is whether the user opens the app in the hour (8 pm to 9 pm) following the randomization of receiving a notification at 8 pm.

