### Time-Varying Covariates

Measured covariates which vary over time within individuals are the use of the modules (Action Planning; Cognitive Bias Re-Training; Self-monitoring and Feedback; Behavioral Substitution; Goal Setting; Normative Feedback; Information About Antecedents); entry of drink (or alcohol-free) record in each session; if the user opened the app before 8 pm that day; and if the user opened the app the day before.

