#### Secondary Analyses (MRT)

Our secondary analyses will assess the effect of sending a notification from the bank of 30 new messages compared to the standard message “Please complete your mood and drinking diaries” on the primary outcome; that is, whether the user opened the app between 8 pm and 9 pm. We will use the same analysis method here as for the primary analyses, which is the estimator for the marginal excursion effect. We will also assess the effect notifications have on users creating an entry to their drinks calendar.

We will investigate the effect moderation of the notification by day in the study, quantified as an interaction, and expressed as a relative risk. We will also examine the sensitivity of the result when day-in-study is replaced by splines or its log-transformation. Lagged notification effects will be similarly quantified.

The continuously valued secondary outcome in the MRT relating to time spent on the app (seconds) will be analyzed using a centered and weighted least-squares estimation method [46] with the effect quantified using the mean difference. All secondary outcomes will be explored by comparing any notification versus none and then separating the two types of notifications.

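### Read literally, the single covariate list makes the lagged-effect analysis adjust for app use that follows the earlier notification, which biases that secondary estimate downward by a few percent

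*Protocol article*

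**What the plan says.** The third item under Secondary Objectives is to "Estimate the lagged effect of prior notifications on near-term engagement". The method appears in one sentence of Secondary Analyses (MRT): "Lagged notification effects will be similarly quantified".

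The covariates are fixed earlier, in Primary Analysis (MRT), and explicitly for secondary analyses too: "Models used in the primary and secondary analyses for the MRT arm will adjust for age, gender, employment type, baseline AUDIT score", followed by days since download and two time-varying terms, "if the user opened the app before 8 pm, and if the user opened the app the day before". Time-Varying Covariates defines these as "if the user opened the app before 8 pm that day; and if the user opened the app the day before". The first is cut off at 8 pm; the second has no time-of-day limit. The primary outcome is "whether the user opens the app in the hour (8 pm to 9 pm) following the randomization of receiving a notification at 8 pm".

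Sequence Generation fixes the daily probabilities at 40%, 30% and 30% and makes them independent of each user's history.

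**The concern.** A covariate is safe to adjust for if it is settled before the randomization whose effect is being estimated. The list meets that test for the day t notification. It does not meet it for the day t−1 notification if it is applied unchanged.

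Two things then go wrong. Opening the app on day t−1 is partly a result of the day t−1 notification, so adjusting for it blocks the most obvious route by which a notification could carry over to the next day. It is also a result of each user's general tendency to open the app, so conditioning on it makes notified and unnotified users differ in that tendency. Both push the lagged estimate downward, towards apparent notification fatigue. The article says it wants to avoid annoying users and names lagged effects as an input to future decision rules, so the direction of the error matters.

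**Working it through.** **Timing.** For outcome day t:

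| Covariate in the list | Relative to the day t notification | Relative to the day t−1 notification |
|---|---|---|
| Opened before 8 pm on day t | before | after |
| Opened on day t−1, any time | before | partly after; includes 8–9 pm on day t−1 |

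**The plan's own figures.** The article gives no figure for the lagged effect. Its only closed-form figure, 372 users per parallel arm, is not an input here. It reproduces closely: (1.96 + 0.8416)² × (0.55×0.45 + 0.65×0.35) / 0.10² = 373.

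**Hand check, lost carry-over.** From the article: effect 2.16, taken as a relative risk. Assumed: an unnotified 8–9 pm opening rate of 0.03 or 0.06; opening multiplies next-day opening by exp(0.4) = 1.4918; no other use of the app.
- Rate 0.03: notified rate 0.03 × 2.16 = 0.0648. Lagged RR = (1 + 0.4918×0.0648)/(1 + 0.4918×0.03) = 1.0319/1.0148 = 1.017.
- Rate 0.06: notified rate 0.1296. Lagged RR = 1.0637/1.0295 = 1.033.
- Within openers, and within non-openers, of day t−1 the ratio is exactly 1.00. Adjustment removes the effect.

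**Hand check, spurious effect.** No lag at all; half the users have rate 0.03 and half 0.06. Among day t−1 non-openers, the high-rate share is 0.94/(0.94 + 0.97) = 0.4921 if unnotified and 0.8704/(0.8704 + 0.9352) = 0.4821 if notified. Next-day rates are 0.03 + 0.03×0.4921 = 0.04476 and 0.03 + 0.03×0.4821 = 0.04446, a ratio of 0.993. Among openers the high-rate share is 2/3 either way, so the ratio is 1.00. The pooled result falls below 1 with no true lag.

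**Simulation.** 25,000 users per scenario, 30 days, notification probability 0.60. The lag-1 log-RR β solves Σ[exp(−βA(t−1))Y(t) − exp(G(t)α)] × (G(t), A(t−1) − 0.6) = 0. G held (a) day only, the randomized contrast; (b) also the two adjusters measured before the day t−1 randomization; or (c) also the two adjusters as literally listed. Assumed: base rate 0.03 or 0.06; SD of latent engagement 0, 0.5 or 1.0; opening raising next-day opening by log RR 0 or 0.4; direct lag log RR −0.10, 0 or +0.15.

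Lag-1 RR, (a) → (c), across both base rates:

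| True lag | RR 2.16, SD 0 | RR 2.16, SD 0.5 | RR 2.16, SD 1.0 | All scenarios, including RR 3.5 |
|---|---|---|---|---|
| None | 0.992–0.994 → 0.992–0.993 | 0.983–0.994 → 0.976–0.979 | 0.987–0.999 → 0.956–0.964 | 0.98–1.00 → 0.91–1.00 |
| Through opening only | 1.004–1.017 → 0.989–0.990 | 1.009–1.027 → 0.979–0.985 | 1.008–1.022 → 0.954–0.970 | 1.00–1.06 → 0.92–1.00 |
| Direct positive | 1.152–1.156 → 1.152–1.156 | 1.144–1.156 → 1.134–1.137 | 1.144–1.152 → 1.098–1.115 | 1.14–1.16 → 1.03–1.16 |
| Both | 1.171–1.186 → 1.151–1.153 | 1.175–1.196 → 1.135–1.145 | 1.165–1.174 → 1.090–1.118 | 1.17–1.24 → 1.03–1.16 |
| Opening plus direct negative | 0.909–0.921 → 0.897 | 0.915–0.926 → 0.886–0.895 | 0.913–0.930 → 0.871–0.881 | 0.91–0.96 → 0.85–0.90 |

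Monte Carlo error is about 0.01 on each level; (a) and (c) come from the same data. Choice (b) matched (a) to within about 0.003 everywhere. The largest shift at RR 2.16 is 1.174 → 1.090, or 1 − 1.090/1.174 = 7%. At RR 3.5, above the design value, it is 1.190 → 1.031, or 13%.

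**At trial size.** A separate simulation used 1200 users, 80 runs per scenario and a base rate of 5% falling 3% per day. With no lag, the literal list gave 0.96–0.99. With carry-over through opening, pre-lag adjusters gave 1.03–1.06 and the literal list 0.96–0.97. In the strongest carry-over scenario, pre-lag adjusters rejected in 32.5% of runs, while the literal list rejected in 15%, all in the wrong direction. With 80 runs the standard errors are √(0.325×0.675/80) = 5 and √(0.15×0.85/80) = 4 percentage points.

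**The case against.** The strongest reply is that the text does not force the biased analysis. The excursion effect is defined relative to a decision day, for a user who "followed the notification scheduled used in the MRT up to day" t−1 and then deviates. An analyst who moved the whole list back to the lagged decision day would have valid covariates and no bias. Alternatively, the sentence on lagged effects directly follows the one on moderation by day, so it could mean that yesterday's notification is tested as a moderator of today's. In that case the list is again pre-treatment. In a check of that model, the interaction RR with the list agreed with the unadjusted contrast to within 0.012 in all six scenarios. It can also be said that a condensed article leaves the indexing of lags to the analysis plan, and that the shifts are small.

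Part of this stands. Both alternatives are possible, and either removes the bias. But the article states neither. The objective's wording points to a main lagged effect, and the covariate sentence covers secondary MRT models without exception. This is a stated rule that misleads if followed, not a detail left out. Smallness cuts both ways: a shift of a few percent is about as large as the lag that carry-over through opening would produce.

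A reader might infer that the primary result is biased too. It is not: both covariates precede the day t randomization. A reader might also infer that any lagged effect would be removed or reversed. The simulations do not support that: a direct positive lag was attenuated or unchanged and never reversed, and a negative one was exaggerated.

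**Conclusion.** The point holds, with moderate severity, for one secondary objective. Applied as written, the list makes the lag-1 model condition on consequences of the day t−1 notification, and the estimate is biased downward. Carry-over through opening is removed and can change sign. A direct positive lag is attenuated or unchanged, and a negative lag is exaggerated. A small spurious negative effect appears when users differ in underlying engagement.

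The direction follows from the timing of the covariates. The size does not come from the document: it rests on assumed base rates, heterogeneity and carry-over, and on a same-day effect held constant over 30 days. The article expects that effect to fade, which would shrink the bias on later days. Under these assumptions and an effect of 2.16, the shift is nil to about 7% on the RR scale. A negative lagged estimate from this model could not safely be read as notification fatigue; nor do the documents show that it would be spurious.

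**What to change.** Limit the list in Primary Analysis (MRT) to same-day effects. Add one sentence to Secondary Analyses (MRT): for the effect of the notification on day t−k, the time-varying adjusters are whether the user opened the app before 8 pm on day t−k and whether the user opened it on day t−k−1, and app use from that decision point onward is not adjusted for. Omitting the time-varying adjusters is equally valid, because the randomization probabilities are fixed and independent of history. Any lagged analysis that does adjust for later use should be labelled a direct-effect analysis that needs further assumptions. If the lag is meant as a moderator of the same-day notification, say so; the list can then stay.

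The cost is one or two sentences and a shifted index in the code. No new data are needed, and the conduct of the trial does not change.

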#### Secondary Analyses (MRT)

Our secondary analyses will assess the effect of sending a notification from the bank of 30 new messages compared to the standard message “Please complete your mood and drinking diaries” on the primary outcome; that is, whether the user opened the app between 8 pm and 9 pm. We will use the same analysis method here as for the primary analyses, which is the estimator for the marginal excursion effect. We will also assess the effect notifications have on users creating an entry to their drinks calendar.

We will investigate the effect moderation of the notification by day in the study, quantified as an interaction, and expressed as a relative risk. We will also examine the sensitivity of the result when day-in-study is replaced by splines or its log-transformation. Lagged notification effects will be similarly quantified.

The continuously valued secondary outcome in the MRT relating to time spent on the app (seconds) will be analyzed using a centered and weighted least-squares estimation method [46] with the effect quantified using the mean difference. All secondary outcomes will be explored by comparing any notification versus none and then separating the two types of notifications.

#### Secondary Analyses (Parallel Arms)

Time to complete disengagement will be analyzed using the Kaplan-Meier estimator. A Cox proportional hazards model will be used to estimate the hazard ratio for disengagement comparing the three parallel arms. The proportional hazards assumption will be assessed graphically and using tests based on Schoenfeld residuals. If nonproportionality is detected, methods allowing for this will be applied and presented as exploratory analyses alongside the previous Cox model analysis.

Linear regression models with robust standard errors will be used to compare the time spent on the app, both overall and on specific modules, between the three parallel trial arms. Similar models will be used to compare the total number of days of app use between arms.

No adjustment will be made for multiple testing. Outcomes and analyses are categorized by the degree of importance (primary and secondary), and results will be interpreted in the light of that ordering.

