### Time-Fixed Covariates

Measured time-fixed covariates are age, gender, type of employment (manual, nonmanual, or other), day of the week of download, and baseline AUDIT score.

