### Sample Size

We aim to randomly assign 1200 users to the MRT arm, 400 users to the standard daily notification arm (Secondary Arm A), and 400 users to the no notification arm (Secondary Arm B), resulting in a total of 2000 participants. The sample sizes were calculated as follows:

To estimate the sample size required for the MRT arm, we used a simulation-based approach to determine the sample size required to attain a prespecified power level, because currently there is no off-the-shelf software to calculate the sample size for MRTs with binary outcomes. Our primary objective is to understand the marginal effect of receiving a push notification at 8 pm on engagement, with an important secondary objective towards the tailoring of the notification policy is identifying effect moderation over time. Plausible estimates of a treatment effect and effect moderation were obtained by exploring patterns of use with *Drink Less*. With 80% power and 5% type I error, we have sized this trial to detect a marginal treatment effect of 2.16, which decays by a factor of 0.911 by day since download. This is close to 100% power for our primary objective, the marginal effect. See Multimedia Appendix 4 for more details.

The sample size of the two additional parallel arms was determined based on the secondary outcome of time to disengagement (no use for seven or more consecutive days). Analysis of the current app shows that 55% of users have disengaged by day 30. We powered this sample size based on a minimal relevant change in disengagement of 10%, such that we expect 65% of users to disengage by day 30 when no notifications are delivered. With a 5% type I error and 80% power to detect an increase in disengagement to 65% of users by day 30, we would require 372 users per arm. To simplify the allocation process, we rounded-up the sample size for the parallel arms to 400 users per arm each, resulting in an overall sample size of 2000 and an allocation ratio of 60% to the MRT and 20% to each parallel arm.

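### The between-arm linear models name no baseline covariates, although the set fixed for the MRT models is collected in every arm: a small efficiency gain is available, not an error corrected

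*Protocol article*

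**What the plan says.** All places are in the protocol article.

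- **Primary Analysis (MRT)** fixes the adjustment set and its scope: "Models used in the primary and secondary analyses for the MRT arm will adjust for age, gender, employment type, baseline AUDIT score". The same sentence goes on to days since download and two recent-use indicators (use earlier that day, use on the previous day).
- **Secondary Analyses (Parallel Arms)** sets out the 30-day comparison. For time to disengagement: "A Cox proportional hazards model will be used to estimate the hazard ratio for disengagement comparing the three parallel arms". For the totals: "Linear regression models with robust standard errors will be used to compare the time spent on the app, both overall and on specific modules". The section covers checks of proportional hazards, robust standard errors and multiplicity, but names no covariates. It does not say that the models are unadjusted either.
- **Time-Fixed Covariates** lists what is available at baseline: "Measured time-fixed covariates are age, gender, type of employment (manual, nonmanual, or other), day of the week of download, and baseline AUDIT score".
- **Data Collection, Management, and Analysis** says that baseline descriptions "will be reported for all MRT participants and participants in the two additional arms".
- **Implementation** describes the allocation: "Simple randomization was used, with no stratification or blocking".
- **Sample Size** plans 1200 users for the MRT and 400 for each parallel arm. The parallel arms are sized for 80% power on disengagement, while power for the primary MRT effect is put close to 100%.

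**The concern.** The article does go down to the level of named covariates, but only for one part of the trial. Followed as written, it gives adjusted MRT estimates and unadjusted between-arm estimates, although four baseline variables are at hand for all users. The between-arm comparison is also the part with less power to spare.

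For a linear model comparing randomized arms, adding prognostic baseline variables leaves the target, the difference in means, unchanged and lowers the residual variance. What is at stake is some precision on total time in the app, time by module and days of use.

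A second, smaller matter is scope. The MRT is itself one of the three arms compared, so a reader could take the adjustment sentence for the MRT arm's secondary analyses to cover these models too. The recent-use indicators would then come in. They are measured after randomization and are affected by the notifications, so they do not belong in a 30-day comparison of arms.

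**Working it through.** **1. The plan's own figure.** Inputs from Sample Size: "Analysis of the current app shows that 55% of users have disengaged by day 30", 65% expected without notifications, 5% type I error (taken as two-sided), 80% power. With unpooled variance,

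n per arm = (0.55 × 0.45 + 0.65 × 0.35) × (1.960 + 0.842)² / 0.10² = 0.475 × 7.849 / 0.01 = 372.8.

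The pooled-variance formula gives 376. The stated 372 is reproduced to within rounding. It concerns a proportion disengaged, not the linear-model outcomes.

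**2. Gain in the linear models.** If the covariates explain a share R² of outcome variance, the standard error is multiplied by √(1 − R²), and the adjusted analysis is worth 1/(1 − R²) times as many users. The article gives no R², so a range is shown. As a reference effect I take the standardized difference detectable with 80% power at 400 per arm:

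d = (1.960 + 0.842) × √(2/400) = 0.198 SD.

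| Assumed R² | SE multiplier | Equivalent users per arm | Power for d |
|---|---|---|---|
| 0 | 1.000 | 400 | 80.0% |
| 0.01 | 0.995 | 404 | 80.4% |
| 0.02 | 0.990 | 408 | 80.8% |
| 0.05 | 0.975 | 421 | 82.0% |
| 0.10 | 0.949 | 444 | 84.0% |

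As ratios of users: 1/0.98 = 1.02, 1/0.95 = 1.05, 1/0.90 = 1.11.

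**3. Cost in parameters.** The four variables need about five model columns: one each for age, gender (taken as binary) and AUDIT score, and two for the three employment categories. With two arms of 400 that is 5/800, or about 0.6% of the users. The cost is negligible, but so is the gain once R² is near that level.

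**4. What the formula does not cover.** The 1/(1 − R²) result is for linear models. The hazard ratio is non-collapsible: adding prognostic covariates to the Cox model moves the target from a marginal to a conditional hazard ratio, and can raise power without narrowing the standard error. The table therefore says nothing about time to disengagement, the outcome that sized the parallel arms.

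**5. Sensitivity to smaller arms.** The Results section reports 452 users by early March 2020. Taking that as 59 to 65 days after the start and extending the pace over the 91 calendar days of the window gives 452/65 × 91 = 633 to 452/59 × 91 = 697 users. One fifth of these is about 127 to 139 per parallel arm. At 138 per arm, power for the same d goes from 37.7% unadjusted to 38.3% (R² = 0.02), 39.3% (0.05) and 41.1% (0.10).

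**The case against.** The strongest reply is that nothing is stated wrongly. The section on the parallel arms is silent on covariates, and a condensed article may leave them to an analysis plan that is not shown. The words limiting adjustment to the MRT may simply reflect a list that includes time-varying terms. An unadjusted comparison of randomized arms is valid, and the outcomes are secondary. The article nowhere says that these baseline variables predict app use. The predictor of engagement that it does cite is perceived usefulness, which is not among the measured baseline covariates.

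Most of this stands. It rules out calling the section an error and makes the size of the gain conditional on an assumed R². It does not remove the point, because the article itself fixes covariates for one set of models and leaves the other without, and the improvement needs no new data.

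Three stronger readings are tempting and are not supported:

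- **That simple allocation leaves an imbalance biasing the arm comparison.** It does not. Chance imbalance is already allowed for in the unadjusted standard errors.
- **That the gain is free and assured.** It depends on an R² that the document does not give, and could be nil.
- **That adjustment would rescue the comparison if recruitment stays slow.** The projection rests on one count at a loosely stated date. Even on that projection, power rises only from 37.7% to 41.1% at R² = 0.10.

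**Conclusion.** The point holds as a minor improvement. The adjustment set is fixed for the MRT models only, the same variables exist in every arm, and the between-arm linear models could use them without changing what they estimate. The benefit is about 2% to 11% more users' worth of information per arm if R² lies between 0.02 and 0.10, and close to nothing below that. It rests on the assumed R² and on two-sided 5% testing, and applies to the linear models only. The analysis as written remains valid, and no primary conclusion is affected.

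**What to change.** In Secondary Analyses (Parallel Arms), or in the analysis plan before the arms are compared, add wording to this effect:

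- The linear models comparing the three arms adjust for age, gender, employment type and AUDIT score at baseline, the set already used for the MRT. The unadjusted estimate is reported alongside.
- No use variable measured after randomization, such as use earlier in the day or on the previous day, enters these models.
- The unadjusted Cox model remains the main analysis of time to disengagement. Any adjusted Cox model is labelled supporting, with a note that its hazard ratio is conditional and so a different estimand.

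The cost is two or three sentences and a few lines of code, with no new data and no change to the trial's conduct. Fixing the choice in advance also prevents a later choice between adjusted and unadjusted results.
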